### Interim analyses {21b}

The Cl will make the final decision to terminate the trial.

### Methods for additional analyses (e.g. subgroup analyses) {20b}

Not applicable

### Methods in analysis to handle protocol non-adherence and any statistical methods to handle missing data {20c}

All randomised participants will be included in the main analyses. An intention-to-treat analysis will be carried out relating to any protocol non-adherence or dropouts. However, due to the nature of the trial very few dropouts are anticipated. Nevertheless, sensitivity analysis will be performed for any of the missing data.

### Plans to give access to the full protocol, participant level-data and statistical code {31c}

Not applicable

## Oversight and monitoring

### Composition of the coordinating centre and trial steering committee {5d}

Not applicable

### Composition of the data monitoring committee, its role and reporting structure {21a}

The data recorded in this study will be stored securely both physically and electronically. The data will be analyzed in the Queen Mary, University of London by the CI of the research student. The data will be password protected and the only the CI and the research student will have full access. The personal data of the participants will be securely held within the research facilities at the Queen Mary, University of London, by the chief investigator.

### Adverse event reporting and harms {22}

We expect no adverse events in the study, as it is questionnaire-based and relates to routine clinical care of MAA therapy in relation to OSA management.

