**Discussion:**

The currently available treatments for obstructive sleep apnoea depend entirely on the patient’s acceptance and use. There are several factors that affect cooperation and wear for example patients’ awareness of their condition, social support and psychological behaviour. In addition, mood, such as anxiety, stress, and depression, may affect wear. At the same time, we know that interventions involving more education and behaviour approaches can help patients adapt more easily to some treatments. As a result, the present trial aims to explore the potential role of these factors to maximise treatment success and minimise side effects.

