Although initial subjective treatment adherence to MAA therapy is relatively high, it is declining over time. A phone-based survey of 69 patients with mild to moderate OSA prescribed MAA, reported a 32% adherence rate after 4 years of therapy, indicating a high level of non-adherence [12]. The study also suggested the prevention of barriers, associated with MAA therapy adherence, to improve the efficiency of the appliance and disease outcome. In a systematic review, Hoffstein et al. (2007) reported a wide range of (4–76%) adherence rates in the first year of appliance use and further studies have highlighted that adherence decreases with time [13]: 83% after 1 year [14] and 62–64% after 4–6 year [15, 16].

MAA adherence might differ depending on the type of the appliance, custom-made or ready-made, disease severity, and perhaps patient management [17]. In a recent systematic review, patient-reported adherence (6.4–7 nights per week and 5–6.3 h per night) and preference (*p* ≤ 0.001) were strongly associated to custom-made MAA in comparison to ready-made MAA [18]. Subjective side effects such as dry mouth, excessive salivation, tooth discomfort, muscle tenderness, and jaw stiffness, have never lead to treatment discontinuation [19–22]. In addition, tooth movement and occlusal changes have been seen in objective measurements after 1 to 4 years of follow-up, but these changes have not been reported as being related to treatment withdrawal [23–27].

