### Trial design {8}

This study is a single-centre, superiority, two-arm, parallel-group, individually randomised clinical trial, with 1:1 allocation, designed to test the effectiveness of stage-matched intervention in enhancing patient adherence to MAA therapy in patients with OSA. In addition, we plan to recruit patients with a confirmed OSA diagnosis, specifically referred for MAA therapy from secondary care.

Ethical approval was obtained from the Greater Manchester West Research ethics committee (REC ref: 19/LO/0972 and 19/NW/0391). Patients meeting the eligibility criteria will be provided with a patient information leaflet explaining the whole study. Interested patients will be asked to sign the informed consent, after which they will be randomly assigned into two groups- intervention care (IC) and standardised care (SC). Only the investigator and chief investigator (CI) will be aware of the participant’s allocation.

Participants will be provided with a sleep diary (Additional file 1) to record their hours of sleep and MAA wear-time, which will give a subjective record of the adherence (duration of usage of MAA). The TheraMon®, a micro-sensor included in the MAA design, will be used for the objective documentation of MAA adherence. TheraMon® calculates the actual wear time by measuring temperature every 15 min and then transforms this information into wear time when the temperature ranges between two specific values. In the present study, this range is defined as 28 °C to 38 °C, which includes the vast majority of intraoral temperature values observed in an individual under normal conditions.

At baseline (T0), part of the routine clinical subject demographics to be collected will include age, gender, body mass index (BMI), and neck circumference. The AHI will also be recorded during the initial screening. Following an oral examination, upper and lower alginate impressions will be taken along with the participant's bite. In addition, participants will be asked to complete the following questionnaires at T (0):
Epworth Sleepiness Scale (ESS)Self-efficacy measure for sleep apnoea (SEMSA) modified for oral appliancePittsburgh Sleep Quality Index (PSQI)EuroQol-5 Dimension (EQ-5D)Socio-economic position questionnaireSocial support scale

The above questionnaires will provide information concerning the participant’s daytime sleepiness, personality, quality of sleep, health-related quality of life, socio-economic status and social support, respectively.

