
At pre-treatment T(1), participants will undergo the initial fitting of the MAA and be provided instruction on use and care.

Both IC and SC groups will be called for follow-up at 3 (T2), 6 (T3), 18 (T4) and 36 (T5) months. Any problems that the patients might be experiencing regarding MAA use will be attended to at these appointments. In addition, data indicating adherence will be collected and evaluated at the appointments both subjectively and objectively by downloading the data from the sensor using dedicated software.

Furthermore, at T(2), participants will be asked to complete the SEMSA questionnaire, whilst at T(3), participants will need to complete the ESS, SEMSA, PSQI and EQ-5D questionnaires.

One-to-one interviews will be conducted 6 months into treatment with both (*n* = 5–10) compliant and non-compliant patients. It will comprise of questions, which will address the following topics:
Patient's awareness of risks and benefits of OSABarriers and facilitators of MAA therapyThe interviews will be conducted face-to-face, recorded, and transcribed by a third-party service (Essential secretary Ltd., UK). However, due to the COVID-19 pandemic, the interviews will take place online (Microsoft® Teams or Zoom cloud meetings) to ensure the participant’s safety. Although, if the participant is comfortable travelling, the interview can be carried out in a private seminar room. Inductive content analysis will be employed to describe the experiences of OSA and MAA therapy of compliant and non-compliant patients without imposing preconceived categories and names of categories to evolve from the data [49].

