### Strategies to improve adherence to interventions {11c}

The study specifically aims to enhance MAA therapy adherence in patients with OSA. The strategies employed to improve adherence to the intervention i.e. the MAA therapy have been designed on the principles on the behaviour change model, HAPA. These strategies are described in detailed in Table 1.

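### The harms section expects no adverse events, which conflicts with the appliance side effects the protocol itself lists, and no systematic recording of them by arm is stated

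*Protocol article*

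**What the plan says.** The section on adverse event reporting and harms {22} is a single sentence: "We expect no adverse events in the study, as it is questionnaire-based and relates to routine clinical care of MAA therapy". It gives no procedure for collecting or reporting events.

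Elsewhere the article describes a trial with more than questionnaires:

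- Trial design {8}: "The TheraMon®, a micro-sensor included in the MAA design, will be used for the objective documentation of MAA adherence". Impressions are taken at baseline and the appliance is fitted at T1. Previous appliance users are excluded under Eligibility criteria {10}, so all participants are new users.
- Background {6a}, on symptoms: "Subjective side effects such as dry mouth, excessive salivation, tooth discomfort, muscle tenderness, and jaw stiffness, have never lead to treatment discontinuation".
- Background {6a}, on objective findings: "tooth movement and occlusal changes have been seen in objective measurements after 1 to 4 years of follow-up". It adds that these changes have not been reported as a cause of withdrawal.
- Follow-up, Trial design {8}: "Both IC and SC groups will be called for follow-up at 3 (T2), 6 (T3), 18 (T4) and 36 (T5) months". Problems with appliance use are to be dealt with at these visits.
- Purpose, section {11c}: "The study specifically aims to enhance MAA therapy adherence in patients with OSA".
- Abstract, Discussion: "the present trial aims to explore the potential role of these factors to maximise treatment success and minimise side effects".

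**The concern.** The harms sentence gives two reasons for expecting nothing, and neither is sound as written. The study is not only questionnaire-based, because a worn device supplies the objective primary outcome. Routine care does not settle the matter either, because what is randomised is meant to change how much the device is worn.

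If the intervention succeeds, participants in the intervention arm will have more hours of appliance exposure because they were randomised to it. Whether side effects rise with those hours then becomes a question about the intervention. With no systematic record in both arms, the trial could report more hours of wear and say nothing reliable about their tolerability. It would also lack a candidate explanation for nights with reduced wear.

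**Working it through.** The harms section contains no figure to reproduce, so the check sets its two reasons against the rest of the article and then looks for any place where side effects are recorded.

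**Reason 1, questionnaire-based.** Trial design {8} and the collection plan {18a} both rely on an appliance with a built-in sensor. Everyone in both arms is fitted with one. The description is inaccurate.

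**Reason 2, routine care.** Both arms receive the appliance as standard treatment ({6b}, {11b}). The null hypothesis, the primary endpoint and {11c} all concern raising nightly hours of wear through the intervention. Routine care therefore accounts for the background level of side effects, but not for a difference between arms that follows from a difference in wear.

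**Timing.** The Background places tooth and bite changes at 1 to 4 years, which is months 12 to 48, a span of 36 months. Follow-up to month 36 covers 36 − 12 = 24 of those 36 months. The visits at 18 and 36 months both fall inside the window.

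**Where side effects could be recorded:**

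| Place | Side-effect item |
|---|---|
| Table 3, follow-up visits at 3, 6, 18 and 36 months | none at any of the 4 |
| Outcomes {12}, primary and secondary | none |
| Collection plan {18a} | questionnaires and sensor adherence only |
| Statistical methods {20a} | none |
| Trial design {8}, follow-up visits | problems attended to; recording not mentioned |
| Trial design {8}, interviews at 6 months | barriers to therapy, n = 5–10, before the 12-month start of the window |

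The nearest substitutes are also uneven between arms. Under Tables 1 and 2 the intervention arm receives four booster calls (weeks 3, 6, 18 and 21) that prompt participants to name barriers to use. The standard-care arm receives none. Incidental mentions of side effects would be elicited more often in one arm.

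**What counts by arm could show.** The sample size section {14} gives 28 per arm. The side-effect rate is not given, so 20% to 50% is an assumption. With the same rate p in both arms, the half-width of a 95% interval for the difference is 1.96 × √(2p(1 − p)/28):

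- p = 0.20: 1.96 × √(0.32/28) = 1.96 × 0.107 = 0.21
- p = 0.50: 1.96 × √(0.50/28) = 1.96 × 0.134 = 0.26

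The precision is about ±21 to ±26 percentage points, which is enough for description only.

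**The case against.** The best defence is that the sentence is about the tested intervention: a pamphlet, video, counselling and phone calls added to a treatment these patients were already referred for. On that reading it says the add-on brings no new adverse events, and known appliance effects belong to routine care. This explains how the sentence came to be written. It does not rescue it, because the add-on works by increasing exposure to the appliance.

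A second defence is that this is a journal article condensing protocol version 04, and that adverse event forms may sit in the full document. That stands as far as it goes. A reader might infer that harms will go unrecorded, but the article does not say so. It supports only the narrower statement that no systematic capture by arm is stated. Forms in a fuller document would still leave the printed rationale in conflict with the Background and the design.

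Two further readings are tempting and are not supported:

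- A reader might infer that the trial loses a main reason for stopping wear. The Background says the subjective effects have not led to discontinuation and that the tooth and bite changes have not been linked to withdrawal. The most that can be said is that side effects might reduce hours per night, which is the primary outcome and can fall without anyone stopping.
- A reader might infer that minimising side effects is a formal aim. The phrase appears only as a closing remark in the abstract. The objectives {7}, the endpoints and the outcomes {12} contain no such aim.

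**Conclusion.** The stated premise of the harms section is wrong on the document's own evidence and should be corrected. Side effects of the appliance are to be expected, every participant is exposed, and exposure is meant to differ between arms. No side-effect item is shown at any of the 4 follow-up visits, 2 of which fall within the period the Background gives for tooth and bite changes.

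The consequence is limited. The primary comparison, the sample size and the adherence analysis do not depend on this sentence. What changes is whether the trial can describe tolerability alongside wear. The conclusion assumes that the article's schedule, outcomes and collection plan reflect the full protocol on this point. If they do not, the conflict in wording remains but the gap in recording may not.

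It would go too far to say that recording side effects would let the trial show that added hours come without added harm. At 28 per arm it would not.

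**What to change.** Rewrite the harms section {22} so that it agrees with the Background {6a}, Trial design {8} and the abstract's Discussion: state that the side effects listed in the Background are expected, and say how they are recorded.

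At T2 to T5, record patient-reported side effects in both arms on the same short fixed checklist, with an item on whether each was linked to reduced wear. Add the row to Table 3. Report counts by arm descriptively, with no claim of equivalence.

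The cost is one form, one table row and a few minutes at visits that already exist in both arms. The limits should be stated alongside: the counts will be imprecise, they cannot establish absence of extra harm, and a checklist does not objectively measure tooth movement or bite change.

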### Frequency and plans for auditing trial conduct {23}

The sponsor or delegate retains the right to audit any study, study site or central facility. In addition, the funders may audit any part of the study where applicable.

### Plans for communicating important protocol amendments to relevant parties (e.g. trial participants, ethical committees) {25}

Any protocol amendments will be communicated to the sponsor (Joint Research Management Office), the relevant research ethics committee and to the study participants.

### Dissemination plans {31a}

It is intended that the results of the research would be presented at conferences or organising/attending workshops. In addition, the results will be published in a peer-review journal.

## Discussion

Not applicable

## Trial status

Protocol version 04, Dated: 31/01/2020

Date recruitment began: December 2019

Approximate date of recruitment completion: September 2021

## Data Availability

Not applicable

## Abbreviations

AHI: Apnoea/Hypopnoea index
CI: Chief investigator
BMI: Body mass index
CPAP: Continuous positive airway pressure
ESS: Epworth Sleepiness Scale
EQ-5D: EuroQol-5 Dimension
HAPA: Health Action Process Approach
IC: Intervention care
MAA: Mandibular advancement appliance
OSA: Obstructive sleep apnoea
PSQI: Pittsburgh Sleep Quality Index
QUIPS: Quality in prognosis studies
SEMSA: Self-efficacy measure for sleep apnoea
SC: Standardised care
T0: Baseline
T1: Pre-treatment
T2: 3-month follow-up observation
T3: 6-month follow-up observation
T4: 18-month follow-up observation
T5: 36-month follow-up observation
